#### Interim analyses {21b}

We plan to include 60 patients, and the trial period for each participant is 26 weeks. This is a non-pharmacological 6-week intervention with no expected adverse or harmful events, and the trial is therefore not subject to independent safety monitoring and periodical review, e.g. interim analyses.

#### Methods for additional analyses (e.g. subgroup analyses) {20b}

We have no intention to conduct subgroup and adjusted analyses.

#### Methods in analysis to handle protocol non-adherence and any statistical methods to handle missing data {20c}

We will apply the analysis framework suggested by White et al. for ITT analysis that depends on making plausible assumptions about the missing data and including all participants in sensitivity analyses [98]. We will:
Attempt to follow-up all randomised participants, even if they withdraw from allocated treatment.Perform a main analysis of all observed data that are valid under a plausible assumption about the missing data (missing at random). Our primary analysis population will be all participants with available data statistically modelled using repeated-measures linear mixed models (see below). These models will be valid if data are missing at random (any systematic difference between the missing values and the observed values can be explained by differences in observed data).Perform sensitivity analyses to explore the effect of departures from the assumption made in the main analysis (data as observed; valid assuming that data are missing completely at random).Account for all randomised participants, at least in the sensitivity analyses. We will analyse all variables with missing data (due to withdrawals) being replaced by imputation of the baseline level, i.e. interpreted as assuming that those who dropped out returned to their baseline level [99]. These models will potentially be valid even if data are ‘missing not at random’ (even after the observed data are considered, systematic differences remain between the missing values and the observed values).

In addition, data will be analysed according to the per-protocol population, where data from participants who participated in a minimum of four out of six sessions of CBT-i are included. The participants from the control group will be considered per-protocol individuals if data are available from all three assessments (baseline, after treatment at week 7, and follow-up at week 26).

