### Criteria for discontinuing or modifying allocated interventions {11b}

If a participant in the intervention group is not able to participate in one CBT-i session due to unforeseen circumstances, an individual session is planned as soon as possible.

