#### Relevant concomitant care permitted or prohibited during the trial {11d}

Participants are prohibited from participating in any professional non-pharmacological treatment for insomnia other than Sleep-RA during the trial period.

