### Outcomes {12}

#### Primary outcome

The primary outcome is SE at week 7 assessed by polysomnography (PSG) [68]. SE percentage = (TST/total time in bed (lights out to lights on)) × 100. In healthy persons, SE is 85–90%.

PSG is a comprehensive study of the biophysiological changes that occur in the human body during sleep. In Sleep-RA, 17 electrodes will be attached to each participant, recording data from electroencephalogram, eye movements electro-oculogram, electromyogram muscle activity or skeletal muscle activation, heart rhythm, respiratory airflow, respiratory effort and peripheral pulse oximetry [69]. All PSG studies will be conducted in the participants’ own homes. Data from PSG will be analysed in epochs of 30 s and managed at the Danish Center for Sleep Medicine (DCSM), Rigshospitalet, Glostrup.

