### Statistical methods

#### Statistical methods for primary and secondary outcomes {20a}

All main analyses will be conducted based on the intention-to-treat (ITT) population. We plan to conduct both an analysis of the full analysis set (patients with outcome data available at baseline) and a per-protocol analysis so that any differences between them can be explicitly discussed and interpreted. The ITT principle states the effect of a treatment policy (i.e. the planned treatment regimen) rather than the actual treatment given. The consequence of conducting ITT analyses is that participants allocated to a treatment group should be followed up, assessed and analysed as members of that group, irrespective of their compliance to the planned course of treatment. Robustness is a concept that refers to the sensitivity of the overall conclusions to various limitations of the data, assumptions and analytic approaches to data analysis. Robustness implies that the treatment effect and primary conclusions of the trial are not substantially affected when analyses are carried out based on alternative assumptions or analytical approaches.

We will control the α level across only the most important hypotheses by use of a hierarchical testing strategy to preserve a type 1 error rate of 5% for the primary outcome of change in SE assessed after treatment at week 7, followed by SE assessed at follow-up after 26 weeks. All the patient-reported outcome measures and other secondary outcome measures will, by principle, only be clinically relevant after 26 weeks. The sleep-related key secondary outcomes (SOL, WASO, TST, insomnia and sleep quality) will only be considered statistically significant with a *P* value <0.01 (0.05/5). The RA-related key secondary outcomes (fatigue, impact of RA and depressive symptoms) will only be considered statistically significant with a *P* value <0.017 (0.05/3) as described in Fig. 2.

In the Sleep-RA trial with repeated measures, participants will be randomly assigned to treatment groups, and outcome observations are made at two time points on each patient. We anticipate that measures on the same patient at different times are correlated and that measures taken close together in time will be more highly correlated than measures taken further apart in time; observations on different patients will be assumed to be independent.

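### The per-protocol set selects CBT-i participants on attendance and controls on complete data, so its difference from the ITT result cannot be read as an adherence effect

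*Protocol article*

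**What the plan says.** All the statements are in the protocol article.

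- **Main population.** Section {20a}: "All main analyses will be conducted based on the intention-to-treat (ITT) population".
- **Purpose of the per-protocol analysis.** The same section plans an analysis of the full analysis set and "a per-protocol analysis so that any differences between them can be explicitly discussed and interpreted". It goes straight on to discuss robustness.
- **CBT-i rule.** Section {20c}: data from "participants who participated in a minimum of four out of six sessions of CBT-i are included". No data condition is stated.
- **Control rule.** Section {20c}: "The participants from the control group will be considered per-protocol individuals if data are available from all three assessments", and the assessments are listed as "baseline, after treatment at week 7, and follow-up at week 26". No conduct condition is stated.
- **Conduct rule for everyone.** Section {11d}: "Participants are prohibited from participating in any professional non-pharmacological treatment for insomnia other than Sleep-RA during the trial period". Section {20c} does not use it in either definition.
- **Missed sessions.** Section {11b}: for a participant who cannot attend one session, "an individual session is planned as soon as possible".
- **Primary outcome.** SE by polysomnography at week 7 (Primary outcome, under Outcomes {12}).

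**The concern.** A per-protocol set should hold participants who did what the protocol asked of them. The control rule measures something else. A control who obtained prohibited insomnia treatment but attended every assessment is in the set. A control who complied fully but missed week 26 is out.

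The control rule also reaches forward in time: an event after week 7 decides whether a control counts in the week-7 comparison. No such condition is stated for CBT-i.

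The two groups are thus selected on different variables, both arising after randomisation, and randomisation no longer makes them comparable. At stake is the use that section {20a} gives to this analysis. If it differs from the ITT result, adherence and selection cannot be separated. If it agrees, the agreement is weak evidence of robustness, because selection and adherence effects could offset each other.

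**Working it through.** **1. The plan's own figures.** With SD 7.5, a difference of 6 points, two-sided 0.05 and a pooled t test (Sample size {14}), the exact noncentral t calculation gives 86.1% power at 30 per arm and 80.7% at 26 per arm. Both match the article. They do not depend on the per-protocol rule.

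**2. The two rules side by side.**

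| Situation | CBT-i | Control |
|---|---|---|
| Week-7 SE present, week 26 missing | kept if at least 4 sessions attended | dropped |
| Used treatment prohibited by {11d}, all data present | kept if at least 4 sessions attended | kept |
| Complied with {11d}, one assessment missing | kept if at least 4 sessions attended | dropped |

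The first and third rows show the asymmetry. The second shows that the one stated conduct rule common to both arms is not used.

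**3. How large could the selection be?** The article gives no attendance rate and no link between attendance or completeness and SE, so every such input below is an assumption. Suppose there is no true effect, SE has SD 7.5, and a participant enters the set when a normal latent variable correlated r with week-7 SE exceeds a threshold that retains a proportion p. The retained mean is then shifted by 7.5 × r × λ(p), where λ(p) = φ(z)/p and z is the standard normal quantile at 1 - p. The spurious difference is

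bias = 7.5 × [r(CBT-i) × λ(p CBT-i) - r(control) × λ(p control)].

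The values needed are λ(0.70) = 0.497, λ(0.80) = 0.350, λ(0.87) = 0.243 and λ(0.90) = 0.195. Control retention of 87% corresponds to the four withdrawals per group allowed in section {14}: 26/30 = 0.867.

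| Attendance | r(CBT-i) 0.3 to 0.5, r(control) 0.1 | r equal in both arms, 0.3 to 0.5 |
|---|---|---|
| 70% | +0.94 to +1.68 | +0.57 to +0.95 |
| 80% | +0.61 to +1.13 | +0.24 to +0.40 |
| 90% | +0.26 to +0.55 | -0.11 to -0.18 |

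For example, at 80% attendance with r = 0.3 against 0.1: 7.5 × (0.3 × 0.350 - 0.1 × 0.243) = 0.61.

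**4. Cases on the other side of zero.** A simulation with a latent prognostic factor, correlated 0.3 or 0.5 with week-7 SE, gave about 0 when neither rule was prognostic, or when both arms had the same retention and the same link to prognosis. It gave -0.28 and -0.46 when only control completeness was prognostic (correlation 0.5 with the factor, 86.7% retained). The formula agrees: the implied r is 0.5 × 0.5 = 0.25, and -7.5 × 0.25 × 0.248 = -0.46.

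**5. Range.** The cases examined run from about -0.5 to +1.7 points. As a share of the 6-point target, that is 0.46/6 = 8% below zero to 1.68/6 = 28% above. These are illustrations, not bounds; a stronger link in the controls would lower the bottom end in proportion. The calculation also leaves out the baseline covariate in the planned mixed model, which would remove the part of the selection that acts through baseline sleep.

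**The case against.** The strongest defence has four parts.

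- **Different rules need not mean bias.** A reader might infer that the set is biased by construction, and in favour of CBT-i because motivated patients attend. The document does not support that. Bias needs attendance or completeness to be prognostic, and to an unequal degree. Patients who improve early might equally stop attending. The individual replacement sessions in {11b} could raise attendance and shrink the effect. This objection stands, so no direction is claimed.
- **Some asymmetry is unavoidable.** Controls have no sessions to attend. This stands for the attendance criterion. It does not excuse requiring complete data of one arm only, or requiring week 26 for a week-7 comparison.
- **Other deviation criteria may sit in a fuller document.** It would be too much to infer that the trial ignores control non-adherence. The point here is narrower: the stated inclusion rules do not use the {11d} prohibition, and the stated control rule is about data rather than conduct. That is text the article fixes, not an omission.
- **Little depends on it.** The primary analysis is an ITT mixed model. A sensitivity analysis imputing baseline values covers all randomised participants, and the per-protocol analysis is an addition. A reader might infer that the trial's main conclusion is compromised; it is not. This limits the consequence but does not repair the comparison that {20a} intends to interpret.

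**Conclusion.** The point holds as a defect in a supportive analysis. The stated rules select the arms on different post-randomisation variables, and the completeness part of the asymmetry is avoidable. A difference between per-protocol and ITT results could not be attributed to adherence.

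The asymmetry itself can be read from the text and needs no assumption. Its numerical effect rests wholly on assumed attendance, retention and correlations, so the range in the working shows only that the effect could be negligible, or a noticeable fraction of the target in either direction. The primary ITT estimate, its type 1 error control and the stated power do not depend on this set.

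**What to change.** Rewrite the per-protocol definition in section {20c}:

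1. Apply one data rule to both arms. Either require the outcome at the visit being analysed, or drop the completeness condition, since the mixed model accommodates missing visits under missing at random.
2. Apply the section {11d} conduct criterion to both arms.
3. Keep the four-of-six attendance criterion for CBT-i.
4. Label the result descriptive, because selection by attendance remains, and say in {20a} that differences from ITT may reflect selection as well as adherence.

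This costs a few sentences and no extra assessments. The existing rule already requires attendance to be known. Use of other insomnia treatment has to be ascertained in both arms for step 2 to work.

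Optionally add, not substitute, a complier average causal effect: randomisation as instrument, attendance of at least four sessions as treatment received, and baseline SE and stratum as covariates. It needs a stated missing-data method, because it cannot retain all 60 participants if week-7 outcomes are missing. Its costs are a wider interval and the assumption that attending fewer than four sessions has no effect.

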#### Plans to give access to the full protocol, participant-level data and statistical code {31c}

The datasets analysed during this trial are available from the corresponding author on reasonable request.

### Oversight and monitoring

#### Composition of the coordinating centre and trial steering committee {5d}

This trial proceeds from COPECARE (Copenhagen Center for Arthritis Research), a multidisciplinary centre which is internationally renowned and provides day-to-day support for the trial. COPECARE represents the steering group in collaboration with the University Hospitals Centre for Nursing and Care Research, Parker Institute and DCSM.

The steering committee consists of health professionals with solid research and management competences. The committee represents knowledge at a high level from different professions: nurses, rheumatologists, psychologist, neurophysiologist and statistician. This ensures scientific quality, multidisciplinary width and possible implementation in clinical practice depending on the results of the trial. The managers of the rheumatology department participate in the steering committee and ensure clinical anchoring and implementation.

Once a year an external assessor from the University of Copenhagen is invited to a meeting with the project management group to discuss progress in the trial and methods to improve quality and stringency.

The daily project manager ([name]) is affiliated to COPECARE. She identifies all potential participants from the recruiting sites through DANBIO (as explained in the “Recruitment” section). She provides oral information and received written consent.

#### Composition of the data monitoring committee, its role and reporting structure {21a}

The intervention in this trial is a non-pharmacological intervention with low or no risk of adverse or harmful events. Therefore, there is no data monitoring committee. The trial is registered on www.clinicaltrials.gov and approved by the Regional Ethics Committee and the Danish Data Protection Agency.

#### Adverse event reporting and harms {22}

Participants will be monitored throughout the period of the intervention to detect any unintended events.

Should a PSG show signs of a sleep disorder requiring further examination or treatment the participant will be contacted by DCSM after the final assessment is completed.

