### Explanation for the choice of comparators {6b}

There are no standards on when and how to identify sleep disturbances in rheumatology outpatient consultations. Participants in the control group will receive usual care on sleep, which in the rheumatology outpatient clinics in The Capital Region of Denmark and in Region Zealand is sporadic and random and conducted via casual conversations based on the general knowledge of rheumatologists or nurses. Participants in the control group will be encouraged by [name] to maintain their usual everyday lives and sleep patterns until follow-up assessment is conducted.

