### Intervention description {11a}

In the Sleep-RA trial, CBT-i is a 6-week intervention with participant attendance of 2 h per week. The intervention will be conducted in groups of two to six participants per group. All sessions will be conducted by [name], who is a trained nurse in CBT-i.

The manual for the CBT-i intervention in Sleep-RA has been developed by [name], [name] and [name] in collaboration with a clinical psychologist trained in CBT-i and patient research partners, in accordance with the “Template for Intervention Description and Replication” checklist and guide [58]. The manual is guided by theory on CBT-i, available evidence and previous CBT-i manuals [54, 59–66]. The CBT-i intervention consists of sleep education, stimulus control, sleep restriction, cognitive therapy and relaxation, as presented in Table 1. The CBT-i intervention includes presentations by [name], exchanges of experiences, assignments, relaxation exercises and individual and shared discussions and reflections on how to use the knowledge gained during the intervention and changed habits related to sleep in daily life.

**Table 1 Tab1:** Cognitive behavioural therapy for insomnia: intervention overview

**Session 1**	Introduction	Presentation
		Goals
		Expectations
	Sleep education	Normal sleep and its determinants
		Sleep needs
		Consequences of insomnia
		Nature of insomnia
		Evaluation of participant sleep
		Sleep hygiene
	Sleep restriction	Introduce sleep diary
**Session 2**	Follow-up	Since last session
	Sleep education	Sleep hygiene
	Stimuli control	Rationale; conditioned arousal
		Instructions
	Sleep restriction	Rationale; sleep drive and sleep consolidation
		Sleep efficiency and sleep window for week 2
	Relaxation	Bed time wind-down
**Session 3**	Follow-up	Since last session
	Stimuli control	Experiences and challenges
	Sleep restriction	Experiences and challenges
		Sleep efficiency and sleep window for week 3
	Cognitive therapy	Cognitions affecting sleep
		Cognitive techniques to treat insomnia
**Session 4**	Follow-up	Since last session
	Sleep restriction	Experiences and challenges
		Sleep efficiency and sleep window for week 4
	Cognitive therapy	Experiences and challenges
		Cognitive techniques to treat insomnia
		Worry-time
	Relaxation	Rationale, break the tension and return to a relaxed state
		Body scan meditation
**Session 5**	Follow-up	Since last session
	Stimuli control	Experiences and challenges
	Sleep restriction	Experiences and challenges

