### Participant timeline {13}

The trial period for each participant is approximately 6 months, and includes 6 weeks of CBT-i for participants in the intervention group and 20 weeks of subsequent outcome assessments for both groups. All participants will complete the same outcome assessments at baseline, after treatment (week 7) and at follow-up (week 26), as presented in Fig. 1 and Table 2.

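### Monitoring for unintended events is tied to the 6-week intervention, not to week 26, and the text does not secure equal ascertainment in the two arms

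*Protocol article*

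**What the plan says.** Adverse event reporting and harms {22} sets the rule: "Participants will be monitored throughout the period of the intervention to detect any unintended events". Its only other provision concerns a sleep disorder seen on polysomnography, about which the participant is contacted after the last assessment.

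The length of the intervention is given in Intervention description {11a}: "CBT-i is a 6-week intervention with participant attendance of 2 h per week". Participant timeline {13} says that the trial period "includes 6 weeks of CBT-i for participants in the intervention group and 20 weeks of subsequent outcome assessments for both groups", and Interim analyses {21b} says that "the trial period for each participant is 26 weeks". Both arms have the same assessments at baseline, week 7 and week 26.

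For controls, Explanation for the choice of comparators {6b} describes usual care on sleep and encouragement to "maintain their usual everyday lives and sleep patterns until follow-up assessment is conducted". Who will be blinded {17a} states that the person delivering CBT-i is not blinded.

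Interim analyses {21b} describes the intervention as one "with no expected adverse or harmful events" and gives this as the reason for having no independent safety review. The data monitoring committee section {21a} gives low or no risk as its reason for having no committee.

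**The concern.** Two things are at issue.

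**The window.** The article states when monitoring takes place, and that period ends long before follow-up does. The key secondary objectives are at week 26, and Statistical methods {20a} treats patient-reported outcomes as clinically relevant only after 26 weeks. Table 1 closes the last session with plans for further work and relapse prevention, so participants are expected to go on using what they have learned. Benefit would be judged at week 26, while unintended events would be sought only up to about week 6.

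**Comparability.** Only one arm has an intervention period. During it, CBT-i participants meet the unblinded therapist every week. No common method of asking about events is stated for the two arms.

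At stake is what the trial can report about harms. With neither a monitoring committee nor a periodic safety review, the rule in {22} is the main stated safeguard. Applied as written, it would give a short record of unintended events that may not be comparable between arms. The efficacy results are not affected.

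**Working it through.** **Inputs**
- Monitoring window: the intervention period (Adverse event reporting and harms {22}).
- Intervention: 6 weeks, one 2 h session per week (Intervention description {11a}).
- Later assessment period: 20 weeks in both groups (Participant timeline {13}).
- Trial period per participant: 26 weeks (Interim analyses {21b}).
- Assessments in both arms: baseline, week 7, week 26 (Participant timeline {13}).

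**Step 1: the plan's own time split.** 6 + 20 = 26 weeks, so {13} and {21b} agree.

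**Step 2: time inside and outside the window.**
- Inside: 6/26 = 23%.
- Outside: 26 − 6 = 20 weeks; 20/26 = 77%.
- If the window is read generously as running to the week 7 visit: 26 − 7 = 19 weeks outside; 19/26 = 73%.

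No other section shown extends monitoring past the intervention. The text of Plans for assessment and collection of outcomes {18a}, which lists data by source, does not mention unintended events. Table 2, the trial schedule, is not shown and could not be checked.

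**Step 3: described trial contacts between baseline and week 7.**

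| | CBT-i | Usual care |
|---|---|---|
| Weekly 2 h sessions | 6 (6 × 2 = 12 h) | none described |
| Contact with unblinded therapist in sessions | yes | none described |
| Same assessment at week 7 | yes | yes |

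Controls still receive treatment for their arthritis and usual outpatient care, so they are not without clinical contact. The protocol does not describe that contact as a route for recording events. It gives neither an event rate nor a method of ascertainment, so no difference in detection between the arms can be calculated.

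**Step 4: what the outcome measures capture.** HADS-D, fatigue scales, pain VAS, MD-HAQ, SF-36, DAS28-CRP and sleep measures are taken in both arms at weeks 7 and 26, with blinded assessors for the examinations and recordings. Worsening on these is recorded. Two limits remain:
- Scale scores do not identify discrete events.
- The Outcomes {12} text under Key secondary outcomes and Other secondary outcomes makes examining these measures conditional on a significant positive effect on sleep efficiency at week 7. After a null primary result the plan does not commit to looking at them.

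**Step 5: after the change.** Coverage rises from 6 of 26 to 26 of 26 weeks. Sample size, power and alpha are unchanged.

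**The case against.** The strongest reply has four parts.

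**The data are largely there.** A reader might infer that harms go unrecorded for 20 weeks. The documents do not support that. Both arms are assessed identically at week 26 on mood, pain, fatigue, function, disease activity and sleep, and polysomnography findings have their own provision in {22}. This stands. The gap is limited to unintended events outside those measures, and to the conditional examination shown in step 4.

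**Unequal detection is not stated.** A reader might also infer that events will be detected unequally. The rule in {22} speaks of participants generally and does not say who asks, how, or that detection runs through the sessions. A condensed article may leave that method to the full protocol. This stands too: unequal detection is a risk that the text leaves open, not a fact that it establishes.

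**The trial makes no safety claim.** No objective is about safety, and 30 participants per arm could not rule out uncommon harms even with full monitoring. That limits the consequence. It does not explain why the stated window should stop 20 weeks before follow-up ends.

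**A change comes late.** Recruitment began on 17 December 2018 and this version is dated 16 January 2020, so some participants may already have passed one or both visits. That is a real cost of the remedy.

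The reply does not remove the window itself. The article fixes that period, so it is not a detail left to another document.

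**Conclusion.** The concern holds in limited form. The stated rule covers 6 of 26 weeks (23%). For the other 20 weeks (77%; 19 weeks or 73% if counted from week 7), discrete unintended events are not sought, although both arms are followed and the key secondary outcomes are judged at week 26. The text also does not secure the same ascertainment in both arms during the covered weeks. How far detection would differ cannot be estimated from the document.

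This assumes that the intervention period means the 6 weeks of CBT-i, as {11a} and {13} describe it, and that nothing in the unshown schedule table extends it. The primary and key secondary efficacy analyses are untouched. The change should be made because it improves the harms information at little cost.

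**What to change.** Amend Adverse event reporting and harms {22} so that:
- unintended events are collected in both arms from randomisation to week 26;
- the same fixed questions are put to both arms on the existing tablet questionnaire at weeks 7 and 26, each covering the time since the previous assessment;
- the answers are tabulated by arm, whatever the primary result;
- events volunteered during CBT-i sessions are listed separately, so that extra contact in one arm does not enter the comparison.

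**Cost.** A few added items at visits that already take place, one table, and slight participant burden. If handled as an important amendment under {25}, it needs ethics approval, notice to sites and an updated registration. The new questions will be available only for participants who have not yet passed the week 7 or week 26 visit. The report should therefore give, by arm, how many were asked at each visit.
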